##### Implicit association task (IAT; [84]

Here the valence version [63] is used (derived from the Inquisit task library [85]). This IAT contains two sets of two word categories. The target words consist of alcoholic drinks (“beer”, “wine, “port, “whisky”, “vodka” and “rum”) or sodas (“Coke”, “Cassis”, “Sinas”, “Spa”, “tonic”, and “juice”). The attribute set consists of positive (“sociable”, “good”, “pleasant”, “nice”, “enjoyable” and “sympathetic”) and negative words (“antisocial”, “bad”, “unpleasant”, “stupid”, “obnoxious” and “tedious”). The Dutch words were matched for prevalence and number of syllables [63]. The stimulus words are presented on a 17 inch laptop (using Inquisit 3 desktop software).

The IAT has nine phases that come in one of two orders. Every phase consists of one practice block and either one or two measurement blocks. Each block consists of 48 randomly selected words. Attribute words (positive or negative) are presented in black (fontsize 14) in the middle of the screen. Feedback appears in red (fontsize 16) below the stimuli words. In case of a wrong response, the word “ERROR” appears on the screen. After responses that are too fast (<150 ms) or too slow (>3 s), feedback follows (“TOO FAST” or “TOO SLOW”) with a warning beep. The category word or words (alcohol or soda words) are presented at the top of the screen, on the left or the right side, depending on the required response (as in Greenwald et al., 1998). The interstimulus interval is 250 ms.

##### Self-efficacy list for drug users (SELD; [54])

The 19-item SELD measures situational abstinence self-efficacy. The authors state that self-efficacy should not be considered a stable quality of a person, but depends on the situation in which the person finds oneself. Three correlated dimensions were found: environmental factors, negative mood and positive mood. SELD scores correlated as expected with severity of drug use. Although it is a reliable and valid instrument to measure self-efficacy in substance users, test-retest reliability and predictive validity remains to be established.

#### Measurements – effects on quality of life

##### EuroQol-5D (EQ-5D; [55]

The EQ-5D is a short (14 VAS scales (0–100)) generic health-related quality of life (HRQOL) patient-report questionnaire which assesses 5 health dimensions (mobility, self-care, usual activities, pain/discomfort and anxiety/depression). Responses in each dimension are divided into three ordinal levels coded: no, moderate or extreme problems. Test-retest reliability and convergent validity are satisfactory in different populations [86,87] but the EQ-5D may show a moderate ceiling effect, thus indices seem less responsive for detecting meaningful clinical differences in alcohol-dependent patients compared to other instruments [88].

##### Community reinforcement approach happiness scale (CRA-HS; [48])

The CRA-HS is a multidimensional instrument that examines a wide variety of life areas on 10-point Likert scales. It forms the foundation of a CRA treatment plan and is used to determine individuals’ current “happiness” in terms of satisfaction or quality of life. It casts light on the severity of problems for each area and subsequently can be used to evaluate treatment outcome by repeatedly assessing changes that occur during treatment. The instrument encompasses life areas such as drinking (or illegal drug use), household, job/education, money management, social life, personal habits, romantic relation, family relationships, legal issues, emotional life, communication, health and general happiness. Preliminary results show that the instrument has overall satisfactory internal consistency and sensitivity to changes over a follow-up period of a month [56]. In addition, scores correlated with the level of rewarding activities.

#### Measurements – safety, acceptability and feasibility of treatment

All regular care providers, EMDR therapists involved in the study, treatment supervisors and physicians have been instructed to report adverse events (AE) and serious adverse events (SAE) which may arise during treatment. At T1 all regular therapists are e-mailed with questions about possible SAE that may have gone unreported between T0 and T1. In addition, all participants are questioned about possible AE and SAE at all time-points. Finally, participants in the EMDR + TAU group keep a daily diary during EMDR treatment in which they are instructed to report (S)AE.

At each time-point participants answer questions about opinions and expectations regarding the treatment (be it TAU or EMDR + TAU) they received, the credibility and burden of treatment. In addition, at the end (completed or not) of each EMDR treatment, the EMDR therapist is required to answer some exit-questions regarding the feasibility of the treatment for this particular participant. More generally, before the first and after the last EMDR treatment in the data collection phase EMDR therapists fill in a questionnaire about their opinions and expectations regarding the EMDR training and supervision, the credibility and burden of treatment.

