## Methods/design

### Design

This study is a randomized controlled trial with two arms: EMDR + TAU versus TAU. The two groups are compared pre-treatment (T0), post treatment (T1 = T0 + 8 weeks) and at follow up one (T2) and six months (T3) post treatment, on variables linked to the research questions. This amounts to a 2 × 4 design with the between factor condition (EMDR + TAU vs. TAU) and within factor time (pre- x post intervention × 1 × 6 months follow-up).

Both groups will be assessed at the same time-points, whereby a substantial part of both groups may still receive TAU at follow-up after 1 month, but may no longer receive TAU at follow-up after 6 months.

The current study is hybrid in that it tries to broaden the generalizability of the outcomes by recruiting a representative, but complex sample while maintaining some of the rigor of efficacy research (e.g. using training and supervision, monitoring of and feedback on treatment fidelity). This allows to analyze data from an effectiveness (outcome in real life circumstances, using all data, including imputed data in case of study drop-out etc.) and an efficacy (outcome under ideal circumstances using only completers data) viewpoint.

The design of this study was approved by the Medical Ethics Committee of Medisch Spectrum Twente and is registered as study NL43892.044.13.

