### Power and sample size calculation

Since two active treatment arms are compared and the sample is expected to be relatively heterogeneous regarding baseline variables such as dependence severity, drinking status and other substance use, it is estimated that the effect size will be relatively small. Clinical relevant differences on the primary outcome variable (changes in number of heavy drinking days in the previous 30 days) were calculated on the basis of data of a recent study [46]. In patients with an alcohol-use disorder referred to in- or outpatient alcohol treatment the mean baseline score for heavy drinking days (≥5 drinks in a single day, over the past 30 days) was 16.33 (SD 11.99). Treatment outcome was such that undertreated patients (<75% attendance of the number of sessions recommended by treatment allocation guidelines, n = 618) showed a reduction of 8.7 heavy drinking days (±12.5) while overtreated patients (>110% attendance of sessions recommended) showed a reduction of 12.5 heavy drinking days (±12.2, n = 362). The difference between under- and overtreated patients is at least 3.8 heavy drinking days over the past 30 days which corresponds to an effect size of *d* = 0.31 or *f* = 0.15).

Subsequent poweranalysis in G*Power version 3.1.2. [47] (ANOVA: repeated measures, within-between interaction) indicated a sample size of 74 to demonstrate this effect (keeping α at 0.05 and power at 0.80 and using 2 groups and 3 measurements (concerning changes in the number of heavy drinking days between 4 time points)). Attrition is estimated to be relatively high at 33%. Therefore we add 26 participants (100 patients in total, 50 in each treatment arm), to meet the required sample size.

To minimize missing values RA1 will use email, text messages, telephone calls, and/or contacts with participants’ regular therapists to remind participants about their assessment appointments. All participants will receive financial compensation of 25 euros (in the form of a gift cheque) for every complete assessment at T2 and T3, regardless of whether or not the participant drops out of treatment.

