### Data collection

Subjects participate in the study for 8 months (from T0 to T3). Patients in both treatment conditions will be assessed identically (see Table 1). Two instruments are only used during the inclusion interview: the MINI-Plus [43] and the MATE 2.1 [44]. At T0, RA1 (blinded to treatment allocation) assesses baseline measurements of all primary, secondary, tertiary and quaternary variables. At T1 (post treatment), T2 (follow-up after 1 month) and T3 (follow-up after 6 months) all but one (the ‘readiness for change’ as measured with the RCQ-D [52] is only assessed at baseline) measurements are repeated by RA1.

For participants in the EMDR + TAU group additional assessments take place within (pre and post levels of distress, craving or positive affect of memory representations on a 11-pt Likert scale) and between (daily diary: number of drinks, intensity and frequency of craving, adverse events) sessions. These assessments are an integral part of the EMDR intervention manual and can therefore only be used to explore changes during the course of EMDR within this group. EMDR therapists also fill in a questionnaire after the last EMDR session of each participant regarding perceived and experienced treatment burden credibility and harm, before, during and after treatment.

RA1 also gathers demographic data: age, sex, social-economic and marital status, educational level, and ethnicity. Participant-report questionnaires (no 3–11 in Table 1 below [6,52-59]) will be provided digitally using Perseus web survey software [60]. The alcohol Timeline Followback interview (TLFB; [61]) is conducted face-to-face by RA1.

The alcohol Stroop [62] and valence IAT [63] will be administered using the program Inquisit 3 [64] for computerized assessment.

After each on-site assessment, participants are referred to a laboratory nearby for collection of blood samples to determine GGT and CDT [65]. Results are interpreted by an independent physician from IrisZorg. The results will be discussed with the participants after the last assessment by this physician, if relevant. In the case that lab results merit intervention before the last follow up assessment, the physician will notify the regular addiction care physician or general practitioner as soon as possible.

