## Discussion

This RCT aims to extend previous findings [15] by including a larger number of participants, using reaction time tasks and bloodsamples in addition to participant-report questionnaires and scales, excludes the principal investigator from treatment and data-collection and uses an outpatient instead of an inpatient setting. A strength of the study is that it is a multi-site trial, enhancing the internal and external validity of the interventions. Another strength is that the exclusion criteria are limited, enhancing the generalizability of findings. In addition, by identifying mediators, moderators and predictors of treatment outcome theoretical models of relapse may be expanded.

The main goal of the study is to determine whether EMDR, when added to TAU, reduces drinking behavior and relapse rates further than TAU only. Even a relative small effect size may be relevant, when achieved with a limited dose of EMDR. In addition, EMDR may provide an important adjunct to current treatment options for patients suffering from craving, negative affect and rumination. In both cases the quality of life is expected to improve.

Finally, the study is aimed at establishing whether the application of EMDR aimed at addiction is feasible and safe in this patient population, even when patients still use substances. Clinicians may be hesitant to use EMDR in this population because they fear triggering craving and subsequent relapse.

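### Regular therapists are actively asked about SAEs only once, at T1; over the remaining six of about eight months, SAEs may go unreported in patients who miss visits, above all those who have left TAU

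*Protocol article*

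**What the plan says.** The section on measurement of safety, acceptability and feasibility describes four sources of SAE information.

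- Standing reporting by regular care providers and EMDR therapists, as well as others: "treatment supervisors and physicians have been instructed to report adverse events (AE) and serious adverse events (SAE) which may arise during treatment".
- One active check with regular therapists: "At T1 all regular therapists are e-mailed with questions about possible SAE that may have gone unreported between T0 and T1".
- Questioning of patients: "all participants are questioned about possible AE and SAE at all time-points".
- A diary in one arm only: "participants in the EMDR + TAU group keep a daily diary during EMDR treatment in which they are instructed to report (S)AE".

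On duration, Data collection states: "Subjects participate in the study for 8 months (from T0 to T3". The Design section places T1 at 8 weeks and T2 and T3 at one and six months post treatment. It expects a substantial part of both groups still to be in TAU at T2, "but may no longer receive TAU at follow-up after 6 months". The TAU section guarantees TAU only up to T1. The power section says: "Attrition is estimated to be relatively high at 33" per cent. The Discussion gives as one purpose of the study to find out whether EMDR aimed at addiction is "feasible and safe in this patient population, even when patients still use substances".

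**The concern.** The T1 e-mail exists because spontaneous reporting can miss SAEs; its own wording says so. The same weakness applies after T1, yet no repeat at T2 or T3 is described. What remains is spontaneous reporting, tied to treatment that may have ended, and questions put to those who attend. A death or a hospital admission can itself prevent attendance, so the patients not asked may be those with the most serious events.

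Two things are at stake. The SAE count for most of the follow-up may be too low. And because the abstract lists safety among the outcomes on which the arms are compared, a difference between arms in loss to follow-up would carry over into the SAE comparison.

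**Working it through.** **Timeline.** Inputs: T1 = T0 + 8 weeks and T3 = T1 + 6 months (Design).

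- T1 = 8 × 7 / 30.44 = 1.84 months.
- T3 = 1.84 + 6 = 7.84 months, which agrees with the stated 8 months.
- Share of follow-up after the only therapist query: 6.0 / 7.84 = 77%.

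**Which routes reach beyond T1.**

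| Route | Window | Condition |
|---|---|---|
| Therapist e-mail | T0 to T1 | None after T1 |
| Standing provider reports | While treatment lasts | Spontaneous; patient must be in care |
| Questions to participants | T0, T1, T2, T3 | Patient must attend |
| Diary | During EMDR | EMDR + TAU arm only |

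The e-mail and the diary drop out after T1. I read the treatment in the standing instruction as including TAU, which is the reading more favourable to the plan.

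**How long the provider route lasts.** The TAU section says that CRA and MDFT typically last 6 months, that CRA can run from 3 to 9 months, that FACT may last much longer, and that participants are already in TAU at enrolment. If a patient has been in TAU for x months at T0, a 6-month course ends 6 − x months after T0. Even at x = 0 that is 7.84 − 6 = 1.84 months before T3. A 9-month course outlasts T3 only if x is below 9 − 7.84 = 1.16 months. So for a typical CRA or MDFT patient the provider route lapses before T3; for FACT patients it may not.

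**Coverage after T1, by type of patient.**

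| Patient | In TAU throughout | TAU ended before T3 |
|---|---|---|
| Attends T3 | Asked at T3 (recall period not stated) | Asked at T3 |
| Attends T2, misses T3 | Asked at T2, then spontaneous reports | Asked at T2, then spontaneous reports until TAU ends, then no route described |
| Misses T2 and T3 | Spontaneous reports only | Spontaneous reports until TAU ends, then no route described |

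The time between T2 and T3 is 5 / 7.84 = 64% of follow-up, so attending T2 alone leaves most of the period without a question to the patient.

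**How many patients.** Inputs: 33% attrition, N = 100 (power section). 0.33 × 100 = 33. Attrition is a single figure, not split by visit, and it does not say how many of those lost are also out of TAU. So 33 is an upper guide to the patients in the lower two rows, and the number in the two cells where no route remains is not known.

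**Direction of error.** If events in unreached patients are missed, the observed risk in an arm is the true risk times the share of events ascertained. The count is then too low in any case. With equal true risks, the ratio of observed risks equals the ratio of the two shares ascertained, so the comparison between arms is distorted only if those shares differ.

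**The case against.** The best case for the plan runs as follows. The instruction to providers has no end date at T1, and many patients stay in care after T1, so an SAE can be reported whether or not the patient attends. Someone who misses T2 but comes to T3 is asked there. A check at T1 fits the period of scheduled EMDR sessions and guaranteed TAU. The fear quoted in the Discussion, that EMDR triggers craving and relapse, is addressed by TLFB, PACS and biomarkers at every time-point rather than by SAE counts. And the text is a condensed article of an ethics-approved study, whose full protocol may say more.

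Much of this stands. A reader might infer that all SAEs after T1 in patients who miss T2 or T3 are lost, or that 33 patients have no SAE enquiry at all. The documents support neither: provider reporting continues while TAU lasts, a later attended visit can recover an event, and 33 is a ceiling. Nor do they define relapse as an SAE, so it should not be used as an example of a missed one.

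Two things are not answered. First, the T0 to T1 limit on the therapist query is a rule the article states, not a detail lost in shortening. Second, the reminders, the gift cheque at T2 and T3, and the contacts with therapists about appointments serve attendance; none is described as an enquiry about SAEs.

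**Conclusion.** The concern holds in a limited form. After T1, which is 77% of follow-up, SAE ascertainment rests on spontaneous reports during treatment and on attended visits. SAEs may go unreported in patients who miss visits, and for a patient who has left TAU and misses T3 no route is described. At most about 33 of 100 patients are affected, on the stated attrition. Under-counting follows if some events in these patients are neither reported by a provider nor recovered at a later visit; bias between arms needs the further condition that loss differs by arm. The documents give no SAE rate and no attrition by arm, so the size of either error cannot be estimated. This is a worthwhile improvement to a stated objective, not a flaw that invalidates the safety data.

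**What to change.** Send the existing SAE e-mail again at T2 and T3, to the current or last regular therapist of every randomised patient, including those who have left TAU or stopped attending, as far as the consent given allows. Staff other than the blinded assessor should send it and handle the replies; the second research assistant, who manages allocation and takes no part in assessments, is one possibility. Report SAEs by arm for all randomised patients over T0 to T3, and state for how many in each arm the SAE status after T1 is unknown.

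The cost is two further standard e-mails per participant, a small burden on therapists and possibly a notice to the ethics committee. The article says that recruitment is under way, so the change can still cover patients not yet past T2 or T3. Its limit is that a dossier may hold little about events after TAU has ended. The fix narrows the gap rather than closing it, which is why the count of patients with unknown status belongs in the report.

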#### Fidelity checks

EMDR therapists receive one full and two half-days of training in the EMDR treatment protocol. All EMDR therapists will be supervised by an EMDR consultant to guide optimal application of the treatment protocol. Monthly, two-hour group supervision supports the EMDR therapist for the whole duration of the data collection phase. Between supervision sessions, the consultant is available for consultation by email. All EMDR treatment sessions will be videotaped. A random selection will be rated for treatment fidelity by several independent raters with EMDRIA approved basic training. Deviations from the protocol will be reported to the consultant and EMDR therapist.

Since participants are randomized and TAU is therefore assumed equal in both groups, no fidelity checks are done regarding TAU.

### Analyses

All analyses will be executed using SPSS. Summary tables will be provided for all baseline, end of treatment and follow-up variables. Data will be summarised using frequency tables (with confidence intervals when applicable), and descriptive statistics (mean, median, interquartile range, number and percentages of participants and two-sided, 95% confidence intervals when appropriate).

Changes in the number of heavy drinking days in the past 30 days will be used to analyze the efficacy and effectiveness of EMDR. Since this primary outcome variable is continuous, a repeated measures ANOVA will be carried out with 2 group (EMDR + TAU versus TAU) and 4 time (pre-, post-treatment, 1 and 6 month follow-up) factors. Randomization stratum will be used as a covariate. Effect sizes will be calculated.

All allocated participants will be included in the primary analysis (intention-to-treat, ITT). Since an ideal ITT requires a complete set of data [89], multiple imputation (or a similar strategy) will be used for missing data, if possible. In addition a per-protocol (PP or completers) analysis will be done. ITT analyses will provide insight into the effectiveness of the treatment in real life whereas PP analysis gives insight into the efficacy or the ability for the treatment to reach its intended effect under ideal circumstances.

Repeated measures of continuous secondary variables such as time to first alcohol consumption, number of total drinks consumed and average drinks per occasion in the past 30 days, severity of the dependence, level of rumination, negative affect, desire thinking, craving, coping self-efficacy, quality of life, biomarkers will be analyzed by carrying out a repeated measures ANOVA with 2 group (EMDR + TAU versus TAU) and 3 (post treatment versus 1 versus 6 month follow-up: time to first drink variable derived from TLFB data) or 4 time (pre- versus post-treatment versus 1 versus 6 month follow-up: all other data) factors.

Distribution of premature treatment termination (PTT), a categorical variable, will be analysed using chi-square tests. A range of baseline clinical characteristics potentially associated with subsequent PTT will be examined. A logistic regression analysis will be conducted to examine the relative contribution of key variables to PTT status. A Kaplan–Meier survival curve will be used to illustrate the distribution of PTT prior to the completion threshold at session 5.

Group equivalence will be analyzed using independent t-tests to compare the experimental with the control group on continuous baseline or pretreatment measures of severity and duration of alcohol dependence, motivation to change, coping self-efficacy, quality of life, craving, desire thinking, rumination, negative affect and biomarker levels of GGT and CDT. Group equivalence of categorical variables, such as level of education, history of other substance use, specific contents of TAU use of anti-craving, abstinence enforcing or other psychoactive medication during the study treatment phase and co morbidity will be analyzed using chi-square tests.

Variables such as use of anti-craving, abstinence enforcing or other psychoactive medication, time-in-treatment, craving, rumination, negative affect and desire thinking at T0, may be used as covariates after determining correlations with other primary and secondary outcome measures.

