*AUDIT* Alcohol Use Disorders Identification Test, *CDT* carbohydrate-deficient transferrin, *CRA-HS* Community Reinforcement Approach Happiness Scale, *DSM-IV* Diagnostic and Statistical Manual – 4th ed., *DTQ* Desire Thinking Questionnaire, *EQ-5D™* EuroQol - 5 dimensions, *GGT* serum γ-glutamyltransferase, *IAT* Implicit Association Task, *M.I.N.I.-plus* M.I.N.I. International Neuropsychiatric Interview-Plus, *PACS* Penn Alcohol Craving Scale, *PANAS-SF* Positive And Negative Affect Schedule – Short Form, *PTQ* Perseverative Thinking Questionnaire, *RCQ-D* Readiness to Change Questionnaire - Dutch version, *SELD* Self-Efficacy List for Drug users, *TLFB* Timeline Followback.

The primary outcome variable is changes in number of heavy drinking days since escalating numbers of heavy drinking days may best reflect a (temporarily) loss of control of drinking behavior, while the other behavioral outcomes could also reflect (to some degree) social or controlled drinking behavior.

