#### Secondary objectives – mediators, moderators and predictors of treatment outcome

To explore mechanisms of change, variables that are potential predictors, mediators or moderators of treatment outcome will be examined (see Table 1). We distinguish:Dependent variables:Psychological (participant report): desire thinking, craving, rumination, negative affect and coping self-efficacy,Psychological (reaction times): alcohol attentional bias and implicit associations towards alcohol cues.Covariates:Measured at baseline: demographic characteristics, time-in-treatment, comorbid psychopathology, alcohol consumption, alcohol dependence severity, other substance use and readiness to change;Measured between baseline and follow-up: completer status, time-in-treatment, treatment intensity, the use of psychopharmaca, anticraving (naltrexone and acamprosate) or alcohol abstinence enforcing medication (disulfuram).

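### The primary ANOVA treats baseline as an outcome level and names no contrast, so its 3-df interaction does not directly estimate the effect on heavy drinking days, and its optional covariates are left open

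*Protocol article*

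**What the plan says.** All references are to the protocol article.

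- **Outcome.** Under the primary objective: "The primary outcome variable is changes in number of heavy drinking days".
- **Model.** Under Analyses: "Since this primary outcome variable is continuous, a repeated measures ANOVA will be carried out", with two groups and "4 time (pre-, post-treatment, 1 and 6 month follow-up) factors". T0 is therefore a level of the outcome. Randomisation stratum is the only covariate fixed for this model.
- **Sizing.** The power section used "ANOVA: repeated measures, within-between interaction) indicated a sample size of 74", "keeping α at 0.05 and power at 0.80", with two groups and three measurements. Analyses does not say which ANOVA term decides. The sizing makes the group-by-time interaction the natural reading.
- **Optional covariates.** The last paragraph of Analyses lists medication use, time-in-treatment and several T0 psychological measures that "may be used as covariates after determining correlations with other primary and secondary outcome measures". No number, threshold or timing of the choice is given.
- **Missing data.** All allocated participants are to be included, and "multiple imputation (or a similar strategy) will be used for missing data, if possible".

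**The concern.** The stated goal in the Discussion is directional: does EMDR added to TAU reduce drinking further than TAU alone? A group-by-time F test with (2 − 1)(4 − 1) = 3 degrees of freedom asks something else, namely whether the two four-point profiles differ in any shape. A significant result would still need an unplanned follow-up comparison to say when, in which direction and by how many days. T0 heavy drinking days, which could be used to reduce residual variance, serves instead as one of the outcome levels.

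The covariate wording adds a second problem. The model behind the primary result can depend on correlations seen in the trial data. The timing of two listed items is also unclear. The phrase *at T0* closes the list and may or may not govern medication use and time-in-treatment. The group-equivalence paragraph speaks of medication during the study treatment phase, and the secondary objectives list time-in-treatment both at baseline and afterwards. A value recorded after randomisation could be changed by EMDR, and adjusting for it could bias the comparison.

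**Working it through.** **1. The plan's own figure.** With the usual noncentral F for this test, λ = f²Nm/(1 − ρ), df1 = m − 1, df2 = (N − 2)(m − 1). Take f = 0.15, N = 74, m = 3, and assume ρ = 0.5 and sphericity, since the article gives neither. Then λ = 0.0225 × 74 × 3/0.5 = 9.99 on 2 and 144 df, and power is 0.806. N = 74 reproduces. Three measurements imply 2 df, whereas the planned analysis has four time levels and 3 df.

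**2. Inputs for the comparison.**
- Difference 3.8 days, SD 11.99, change SDs 12.5 (n = 618) and 12.2 (n = 362), all from the power section.
- Pooled change SD = √[(617 × 12.5² + 361 × 12.2²)/978] = 12.39.
- With equal variances, ρ = 1 − 12.39²/(2 × 11.99²) = 0.47. Range tried: 0.3 to 0.7.
- Assumed: compound symmetry, two-sided 5%, n per arm 37 or 50.

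**3. Planned interaction, 3.8 days at T1, T2 and T3.** The arm differences are (0, 3.8, 3.8, 3.8), with sum of squared deviations 0.75 × 3.8² = 10.83. λ = (n/2) × 10.83/[11.99² × (1 − 0.47)].
- n = 37: λ = 2.63 on 3 and 216 df, power 0.24.
- n = 50: λ = 3.55, power 0.32.

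The drop from 0.81 arises because f = 0.15 in step 1 implies a much larger λ than 3.8 days does. That is a separate sample-size matter. Steps 3 to 5 put every test on the same 3.8 days.

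**4. T0-adjusted 1-df contrast on the mean of T1 to T3.** Residual variance = 11.99² × [(1 + 2ρ)/3 − ρ²] = 143.76 × 0.4258 = 61.2, SD 7.82.
- n = 37: SE = 7.82 × √(2/37) = 1.82, noncentrality 3.8/1.82 = 2.09, power 0.54.
- n = 50: SE = 1.56, noncentrality 2.43, power 0.67.

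A simulation of 20,000 trials at n = 37 gave 0.239 (interaction) and 0.536 (contrast).

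**5. How far this depends on assumptions.**

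| Scenario (ρ = 0.47 unless stated) | Planned 3-df test | T0-adjusted mean of T1–T3 |
|---|---|---|
| Sustained, n = 37 | 0.24 | 0.54 |
| Sustained, n = 50 | 0.32 | 0.67 |
| Sustained, ρ = 0.3, n = 37 | 0.19 | 0.52 |
| Sustained, ρ = 0.7, n = 37 | 0.41 | 0.68 |
| Sustained, ρ = 0.7, n = 50 | 0.53 | 0.80 |
| Sustained, AR(1), n = 37 | 0.18 | 0.46 |
| Fading to a third (3.8, 2.5, 1.3), n = 37 | 0.19 | 0.28 |
| Fading to zero (3.8, 1.9, 0), n = 37 | 0.22 | 0.18 |
| T1 only, n = 37 | 0.24 | 0.11 |

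For a sustained effect under compound symmetry the ratio runs from 2.8 to 1.7 at n = 37 and from 2.7 to 1.5 at n = 50 as ρ goes from 0.3 to 0.7. A T0-adjusted contrast at a single visit gives 0.33 at n = 37, 1.4 times the planned test. A T0-adjusted joint 3-df test of T1, T2 and T3 gives about 0.37 for the sustained pattern at n = 37. So part of the gain comes from the adjustment and part from using one degree of freedom.

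**The case against.** **The gain depends on the pattern over time.** This stands. The article gives no correlation and no expected time course, and its Design section says TAU may continue at one month but have stopped by six, so a flat effect cannot be taken for granted. A reader might infer that the change doubles power in general. The table shows that it does not.

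**A two-sided 1-df test gives the same p-value for benefit and harm.** True, but it comes with one signed estimate in days and a confidence interval, which a 3-df F test does not.

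**The deciding contrast and the covariance structure may be in an analysis plan that is not shown.** Fair for such detail. But the article itself makes T0 an outcome level, sizes the interaction and permits covariate choice from outcome correlations.

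**Stronger readings that the text does not support.**
- *Completer status and treatment intensity enter the primary model.* The words "Measured between baseline and follow-up: completer status, time-in-treatment, treatment intensity" stand under the secondary objectives, on mechanisms of change. Analyses fixes only stratum for the primary test and names neither variable among the optional covariates.
- *The covariate wording inflates the type I error.* The choice is tied to correlation with outcomes, not to the treatment p-value. Simulating a choice of the two of six baseline covariates most correlated with outcome gave 4.6%, against 4.8% unadjusted (4,000 trials, N = 74). The issue is prespecification.
- *A third of patients will drop out of the intention-to-treat analysis.* The plan includes all allocated participants through imputation or a similar strategy. The qualifier is loose, but that loss would require every such strategy to fail.
- *The outcome will be mostly zeros.* It is a count from 0 to 30, but the article gives no expected proportion of zeros.

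**Conclusion.** The point holds in a limited form. The planned primary test is an omnibus interaction with baseline as an outcome level. It does not directly estimate the effect the trial is about, and the optional covariates and their timing are not fixed. That the interaction decides is inferred from the power section.

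The size of the benefit rests on SD 11.99, compound symmetry, moderate correlation and an effect of 3.8 days at every follow-up visit. Under those conditions the averaged baseline-adjusted contrast has roughly twice the power. Outside them the gain is smaller or becomes a loss. Nor is this a cure for the sample size: at ρ = 0.47 the contrast reaches 0.54 to 0.67, and 0.80 is reached only at ρ = 0.7 with all 100 patients contributing.

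**What to change.** - Make the primary analysis a linear mixed model on T1, T2 and T3 with group, visit, group-by-visit, T0 heavy drinking days and randomisation stratum.
- Pre-name one 1-df baseline-adjusted group contrast as primary, for example the mean of T1 to T3, and report the estimate and interval at each visit. If the effect is expected mainly at one visit, name that visit instead.
- Fix all covariates before unblinding. State that medication use and time-in-treatment are taken up to T0 only, and keep every post-T0 variable out of the primary effect model.
- Keep multiple imputation and remove the conditional wording. A mixed model alone would omit allocated patients with no follow-up, whom the plan promises to include.

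**Cost.** No new data or patients are needed, and SPSS can fit the model. But this changes a published primary analysis while recruitment is under way. It needs a dated amendment made blind to outcome by arm, with the power statement rewritten for the new contrast. The statistical price is lower sensitivity to an effect confined to one visit or fading to zero.
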